**Measurement**

Progress toward outcomes will be measured utilizing standard, validated instruments (Table 2). Some are available in Spanish and others will be translated and back-translated by the project team. A description of the outcome and measurement instruments follows.

**Tab S2.** Summary of assessment measures

| **Assessment** | **Assessment method and participants** |
| --- | --- |
| Demographic characteristics and anthropometric measurements | Questionnaire on sociodemographic characteristics (father)  Self-reported birthdate and sex (adolescent)  Height, weight measurements^59^ (father/adolescent) |
| Dietary behavioral outcomes | 24-hour dietary recall interviews using Nutrition Data System for Research software^54, 55^ (adolescent)  Food Behavior Checklist^57, 58^ (father)  Skin carotenoid scores assessed with reflection spectroscopy (Veggie meter)^56^ (father)  Frequency of family meals^64^ (father/adolescent) |
| Physical activity and screen time-related behavioral outcomes | Physical activity frequency questions from several sources^61, 62^ (adolescent)  Physical activity questions (time estimate) (Godin-Shepherd Leisure-Time Exercise Questionnaire)^61^ (father)  Screen time questions (time estimate)^62^ (father/adolescent) |
| Parenting practices outcomes | Father parenting practices measures^28^ for fruit, vegetable, sugar sweetened beverage, sweets/salty snack and fast food intake, physical activity and screen time (father/adolescent) |
| Father specific influences on adolescent dietary intake | Father meal/food involvement (planning, buying, preparing with child - created for trial) (father/adolescent)  Father self-efficacy questions for promoting healthy eating and physical activity^65^ (father)  Parenting styles questions^67-69^ (father/adolescent)  Communication^66^ (father) |
| Home food environment | Home food availability questions from Project EAT^63^(father/adolescent) |

Youth will participate in 3 24-hour dietary recall interviews^37^ using Nutrition Data System for Research (NDSR) software version 2016^38^ to assess change in intake of low energy dense foods (fruits and vegetables) and high energy dense foods (sugar-sweetened beverages, sweets/salty snacks, and fast foods). Recalls will be collected in-person during the in-person data collection sessions, followed by 2 recalls by phone within the next week. Recalls will be collected on 3 non-consecutive days including 2 weekdays and 1 weekend day. A food amounts booklet will be provided to help adolescents identify quantities consumed. Skin carotenoid levels will also be assessed using reflection spectroscopy with a Veggie Meter as a biomarker of vegetable and fruit intake.^39^ Fathers will complete the Food Behavior Checklist developed and tested for low-income, low literacy adults^40, 41^ to assess intake frequency of fruits, vegetables, sugar sweetened beverages, sweets/salty snacks, and fast food.

Height and weight will be assessed according to established anthropometric methods^42^ using a stadiometer (model: Seca 202, Hanover, MD) and a digital weight scale (model: Tanita BWB-800P Digital Medical Scale, Arlington Heights, IL, USA) to assess whether BMI changes over time among the intervention vs. control group. Three measures of both height (to the nearest 0.1 cm) and weight (to the nearest 0.1 kg) will be collected and averaged. BMI percentiles and z-scores for adolescents will be generated using a SAS program created by the Centers for Disease Control and Prevention.^43^

Adolescent physical activity will be assessed by a question “In a usual week, how many hours do you spend doing the following activities” in three categories [(1) vigorous exercise, (2) moderate exercise, (3) mild exercise].^45, 46^ Each category will include response options to quantify time with specific examples for activities in each category. Adolescent sedentary behaviors will be assessed using two media use questions from the Project EAT survey:^46^ “In your free time on an average weekday, how many hours do you spend doing the following activities?” and “In your free time on an average weekend day, how many hours do you spend doing the following activities?” for 4 activities: (1) watching TV/DVD/Videos, (2) using a computer (not for homework), (3) playing electronic games while sitting, and (4) using smartphones or tablets. Response options for each activity will quantify sedentary time. Father physical activity level will be assessed using the Godin-Shephard Leisure-Time Physical Activity Questionnaire^45, 47^ based on the question “How many times on average do you do the following kinds of exercise for more than 15 minutes during your free time in a week?” with a blank line to write a number based on times per week for each category: strenuous exercise, moderate exercise, and mild exercise. A validation study showed adequate correlations between questionnaire results and percentile VO_2_ max and percentile body fat and acceptable test-retest reliability.^45^ Father screen time will be assessed in the same manner as adolescents.^46^

Fathers and youth will complete questionnaires to assess frequency of paternal modeling, availability and expectations regarding fruit, vegetable, sugar-sweetened beverage, sweets/salty snacks and fast-food intakes based on existing questions tested for criterion validity.^28^ Assessment of the home food environment will be made to measure change in availability of healthy and less healthful foods^48^ as an indication of paternal food parenting practices. Family meal frequency which provides opportunity for father meal involvement will be measured using a single frequency item regarding frequency of eating meals together with family members.^49^ Change in confidence (self-efficacy) for promoting healthy eating and physical activity among adolescents will be assessed among fathers (completely disagree = 1 to completely agree = 5) using questions analogous to those used in the previous Aventuras Para Ni$ñ$os parent survey based on acceptable internal consistency.^50^ Father-youth communication will be assessed using a14-item parent-youth communication scale validated with a low-income largely African American population will be adapted and translated to Spanish.^51^ Parenting style will be assessed with survey items of general parenting primarily adapted from the Parenting Style Observation Rating Scale for Latino parents with additional items from the Parenting Style and Dimension Questionnaire and the Comprehensive General Parenting Questionnaire.^52-54^

At baseline only, a brief demographic questionnaire will be completed by fathers and adolescents to obtain information regarding age, sex, Hispanic/Latino heritage, years in the U.S., country of birth, household composition, education, employment, and participation in food assistance programs.

## **Safety considerations**

Procedures for recording and reporting adverse events and their follow-up will be developed. The project coordinator will collect information and manage reports.

## **Follow-up**

Outcome data will be collected at baseline (prior to session 1), immediate post-intervention (after session 8), and 3 months post-intervention to determine changes in youth EBRBs and weight status, and paternal parenting practices.

## **Data management**

First, data will be collected using paper-copy surveys, Qualtrics surveys, Veggie meter, and NDSR software in each study site. After each data collection, all of the data components will be entered by undergraduate students and cleaned and compiled by a graduate student.

1. **Description of Master Data File**

Baseline, post, and follow-up data of adolescents, fathers, and mothers and codebooks for adolescents' datasheets and fathers’ and mothers’ datasheets will be stored separately into sub sheets in the master data file. Adolescent baseline, post-, and follow-up datasheets will include survey data, intake data (collected by using NDSR), height/weight and birthdate data, and beta carotenoid scores data (collected by veggie meter), group assignments and randomization, and session attendance. Fathers’ and mothers' baseline, post-, and follow-up datasheets will include survey data, height/weight and birthdate data, and beta carotenoid scores data (collected by veggie meter), group assignments and randomization, and session attendance.

1. **Paper copy survey data**

Undergraduate and graduate students will enter the paper copy survey data twice into the two identical sheets in the excel file. A graduate student will compare these two identical sheets in the SAS and identify the data entry errors. For the unmatched variables, the graduate student will check the paper copy of the data and correct these variables on the sheet. These corrections will be logged into a tab named “Changes in compiled data” in the master data file. After all of the cleaning is done, the graduate student will compile the data into the data sheets of the master data file in the G-drive.

1. **Qualtrics survey**

Qualtrics data will be downloaded as a text format from Qualtrics. Based on the codebook of the datasheet, all of the options (text form) will be changed to the numeric form by using the find & replace function of excel. Finally, cleaned data will be compiled into the data sheets of the Master data file.

1. **NDSR food recall cleaning and compiling**

For the recalls, adolescents will be asked to report all foods, beverages, and water that they consumed in the last 24 hours. A Food Amounts Booklet will be provided to assist in estimating amounts consumed. All of the recalls will be reviewed by an NDSR certified person (either a graduate student or project coordinator) for data entry error. If there are any data entry errors, these errors will be corrected by the NDSR certified person. After this step, NDSR output files will be produced, and these files will be used in the SAS software to obtain intake data. In the SAS software, intakes will be averaged across the number of recalls, and unreliable recalls will be identified and deleted from the output data files. When all of the cleaning processes is done, NDSR recalls will be used to produce five food groups: fruit intake (servings per day), vegetable intake (servings per day), sugary drink intake (serving per day), sweets/salty snacks intake (serving per day), and fast-food intake (serving per day). The food components that comprised each NDSR food group are shown in Table 3. These five groups' intake data will be compiled into the data sheets of the master data file. Children’s HEI scores will be also calculated by using SAS software with NDSR output files.

**Tab S3.** NDSR food groups and their components.

| **Food groups** | **Food categories** |
| --- | --- |
| Fruit intake | Citrus juice  Fruit juice excluding citrus juice  Citrus fruit  Fruit excluding citrus fruit  Avocado and similar fruit  Fruit-based savory snacks |
| Vegetable intake | Dark-green vegetables  Deep yellow vegetables  Tomato  White potatoes  Other starchy vegetables  Legumes (cooked dry beans)  Other vegetables  Vegetable juice |
| Sugary drink intake | Sweetened soft drinks  Sweetened fruit drinks  Sweetened tea  Sweetened coffee  Sweetened coffee substitute  Sweetened water |
| Sweets/salty snacks | Meat-based savory snack  Frozen dairy desert  Frozen non-dairy desert  Pudding and other dairy desserts  Sugar  Syrup, honey, jam, jelly, preserves  Sauces, sweet-regular  Sauces sweet-reduced fat/reduced calorie/fat-free  Chocolate candy  Non-chocolate candy  Frosting or glaze  Vegetable-based savory snack  Crackers- whole grain  Crackers- some whole grain  Crackers- refine grains  Ready-to-eat cereal (presweetened)- whole grain  Ready-to-eat cereal (presweetened)- some whole grain  Ready-to-eat cereal (presweetened)- refined grain  Cakes, cookies, pies, pastries, Danish, doughnuts, cobblers – whole grain  Cakes, cookies, pies, pastries, Danish, doughnuts, cobblers – some whole grain  Cakes, cookies, pies, pastries, Danish, doughnuts, cobblers – refined grain  Snack bars- whole grain  Snack bars- some whole grain  Snack bars- refined grain  Snack chips- whole grain  Snack chips- some whole grain  Snack chips- refined grain  Popcorn  Flavored popcorn |
| Fast food | Fried vegetables  Fried potatoes  Fried chicken – commercial entrée and fast food  Fried fish - commercial entrée and fast food  Fried shellfish- commercial entrée and fast food |

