**Intervention implementation**

The program will be implemented at collaborating sites in a staggered fashion with recruitment by community sites/agencies that are known and trusted within the Latino community including community-based organizations, extension sites, public schools and churches to enhance recruitment and retention.^36^ Collaborating sites will be reimbursed for their staff time to participate in the project including a parent-trainer who will lead the implementation of the intervention and a site recruitment coordinator. Staff who lead the curriculum sessions are expected to be bilingual Latino fathers themselves and will undergo training regarding parenting practices involved in youth EBRBs and instructional strategies about teaching and learning including group management. Participants will be compensated with cash or gift cards to maximize recruitment and retention.

Twenty (20) parent/youth dyads will attend each of six series of eight weekly sessions. Outcome data will be collected at baseline (prior to session 1), immediate post-intervention (after session 8), and 3 months post-intervention to determine changes in youth EBRBs and weight status, and paternal parenting practices.

The study statistician will use SAS to generate separate randomization schedules for each site. The randomization schedules will be created with randomized blocks of 2, 4, and 6. Within each block, assignments will be balanced between Intervention and Control to ensure approximately equal group size if the complete randomization schedule isn't used.  Random assignments will be printed on colored paper slips, folded 3 times and placed in sequentially numbered opaque envelopes to be distributed to enrolled families by the project coordinator. Eventually, father and youth dyads will be randomized (following block randomization procedures) to intervention or control conditions following completion of outcome data assessments at baseline.

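### Staff who can know the arm may correct and delete the dietary recalls behind the five intake outcomes, and no masking or recall log is described

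*Protocol*

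**What the plan says.** The Protocol sets out the recall workflow in some detail.

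- **Review and correction** (Data management, NDSR food recall cleaning and compiling). Every recall is "reviewed by an NDSR certified person (either a graduate student or project coordinator) for data entry error", and where errors are found, "these errors will be corrected by the NDSR certified person".
- **Deletion** (same item). The output files then go to SAS, where "intakes will be averaged across the number of recalls, and unreliable recalls will be identified and deleted from the output data files". The person who decides is not named.
- **Derivation** (same item). "When all of the cleaning processes is done, NDSR recalls will be used to produce five food groups", and those intakes are then compiled into the master data file.
- **Allocation** (Intervention implementation). Assignments sit in "sequentially numbered opaque envelopes to be distributed to enrolled families by the project coordinator".
- **Storage** (Data management, Description of Master Data File). The adolescent sheets for each wave hold the survey, intake and anthropometric data together with "group assignments and randomization, and session attendance". The opening of the section has a graduate student clean and compile all components after each data collection.
- **Log** (Data management, Paper copy survey data). Corrections to paper surveys go into a dedicated tab. No equivalent is described for recalls.

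The Protocol does not say that anyone who handles recalls is masked to group.

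**The concern.** Correcting a recall, or judging it unreliable, is a decision about an outcome value. If the person deciding can know the arm, decisions may differ between arms without any intent: a high SSB day may look less plausible in a child who has just attended the session on sugary drinks. With no log, nothing would later show whether deletions were balanced.

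All five food-group intakes come from these recalls. They are among the primary outcomes in Statistical analysis, and SSB intake by recall is the only outcome with a power statement. Under intention to treat, arm-related editing biases the comparison directly, and neither covariate adjustment nor multiple imputation repairs it.

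**Working it through.** **Who can know the arm, and when**

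1. The coordinator distributes the envelopes and is one of the two roles named for recall review. Randomisation follows the baseline assessments, so the exposure is clearest at the post-intervention and 3-month waves.
2. The other role named for review is a graduate student, and a graduate student also compiles all data. The text does not say whether this is the same person. Compilation follows each data collection, so baseline sheets carrying allocation can already exist when later recalls are cleaned.
3. The deletion step has no named decision-maker, and no masking is stated for it.

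**The plan's own figure**

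Inputs from Statistical analysis: 120 dyads per group, 20% attrition, 0.5 SD, 90% power, two-sided alpha 0.05.

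- Evaluable per group: 120 × 0.80 = 96.
- Required per group: 2 × (1.960 + 1.282)² / 0.5² = 84.1, so 85. Allowing for attrition, 85 / 0.80 = 106.3, so 107.
- Power with 96: Φ(0.5 / √(2/96) − 1.960) = Φ(1.504) = 93.4%.

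The stated 90% is met with some margin. This sets the scale and has no bearing on the workflow point.

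**Size of a one-sided deletion (illustration)**

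The Protocol gives no deletion rate and no variance components, so these are assumptions: three normally distributed recalls per child; within- to between-person variance ratio λ of 1 to 4; the highest recall deleted in a fraction f of one arm and none in the other; SD taken as that of the three-recall mean; no baseline adjustment.

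- Expected highest of three standard normal values: 3 / (2√π) = 0.846. Deleting it lowers the mean of the other two by 0.846 / 2 = 0.423 within-person SD.
- Shift = f × 0.423 × √λ / √(1 + λ/3).
- Example, f = 0.20 and λ = 4: 0.20 × 0.423 × 2 / 1.528 = 0.111 SD.
- Rejection rate with no true effect: shift divided by √(2/96) = 0.1443, then both tails beyond 1.960. For 0.111 SD the standardised shift is 0.77 and the rate 12.0%.

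| f in one arm | Shift (SD), λ = 1 / 2 / 4 | Share of 0.5 SD | Rejection rate with no effect |
|---|---|---|---|
| 5% | 0.018 / 0.023 / 0.028 | 4% to 6% | 5.2% to 5.4% |
| 10% | 0.037 / 0.046 / 0.055 | 7% to 11% | 5.7% to 6.7% |
| 20% | 0.073 / 0.093 / 0.111 | 15% to 22% | 8.0% to 12.0% |

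A cruder assumption gives the same order of size. If a share q of one arm's recalls, lying h SD high, is dropped, the mean moves by q × h / (1 − q). With q = 0.02 and h = 1.5 this is 0.031; with q = 0.05 and h = 2 it is 0.105. These are in SDs of a single recall, so they are not directly comparable with the table.

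**The case against.** The case on the other side is substantial, and several stronger readings fail.

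- **A reader might infer that averaging comes before deletion, so that bad recalls stay in the mean.** The two steps are joined by a plain conjunction, and the next sentence derives the food groups after all cleaning. The wording is loose, but no wrong sequence is established. Only if it were followed literally would one bad recall of three keep a weight of 1/3.
- **A reader might infer that recalls are corrected on the sheet that shows group.** They are not. Correction happens before the output files exist, and intakes reach the master sheets afterwards. The exposure comes from roles and access.
- **A reader might infer that the coordinator deletes recalls.** The text limits the named reviewer to data entry errors, makes the coordinator one of two options, and does not link that role to deletion.
- **Handing out opaque envelopes does not prove knowledge of their contents.** This stands. The supportable statement is that the coordinator can come to know the arm, and that nothing prevents it.
- **A reader might infer that every primary outcome is exposed.** Physical activity and screen time come from questionnaires, and BMI from measured height and weight.
- **A reader might object that a simple mean over-weights the single weekend day.** The 1/3 against 2/7 applies equally to both arms and creates no arm bias. Weighting 5:2 is a preference, and it is undefined when the weekend recall is missing.
- **A reliability criterion is commonly left to the SAP, which is not shown.** Agreed: its absence alone is no finding.
- **The illustration is a worst case,** with all deletions high and all in one arm. Nothing in the Protocol suggests such rates.

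What remains is the workflow that the Protocol does fix: named roles and a shared data file that leave arm-aware correction and deletion possible, with no trail described.

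**Conclusion.** The point holds in this limited form. As written, the workflow allows people who can know the arm to correct the recall-based primary outcomes, and allows recalls to be deleted without masking or a described log. It does not show that this happened or would happen.

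The bias cannot be sized from the Protocol. Under one-arm deletion of the highest recall it is about 0.02 to 0.11 SD, at most roughly a fifth of the planned 0.5 SD. The upper end needs deletions in about 20% of one arm; at 5% the effect on type I error is negligible. The change is worth making because it is cheap and protects the one powered outcome, not because a large bias has been demonstrated.

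**What to change.** 1. Keep group assignment and session attendance in a separate file, and merge it only after recall cleaning is locked. The lock should follow a site's 3-month wave; merging after baseline would expose allocation again when later recalls are cleaned.
2. Give recall review, correction and deletion to an NDSR certified person who has no access to that file and does not distribute allocations.
3. Reword the NDSR cleaning item so that unreliable recalls are removed by a fixed rule before intakes are averaged. The rule itself may stand in the SAP.
4. Extend the existing correction log to recalls, and report corrections and deletions by arm after lock.

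**Cost.** One file is split and an existing task is reassigned. The coordinator can no longer share the review, and compilation of the allocation data waits until lock. If the graduate student who compiles the master file is also the reviewer, access to allocation and attendance must be withheld from that person until then. The Protocol does not say how many certified staff there are, so whether the remaining reviewers can absorb the work needs checking. Masked cleaning does not remove reporting bias from participants who know their own group.

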## **Statistical analysis**

During the planning year, focus group interviews will be audio recorded and transcribed verbatim. A codebook will be developed, and transcripts will be coded by two independent project team members. A software program (NVivo v.12, QSR International (Americas) Inc., Burlington, MA) will be used to organize and enable analysis of coded transcripts. Facilitators and barriers to youth EBRBs and parenting practices will be identified using content analysis procedures based on recurring themes.^55^

Father and youth dyads assigned to the intervention condition (n = 120 dyads) will participate in the program immediately, while father and youth dyads assigned to the delayed-control condition (n = 120 dyads) will participate in the prevention program after the 3 months post intervention data collection session. This will allow detection of an effect size of 0.5 standard deviations in sugared-sweetened beverages (SSBs) 24-hr dietary recall with 90% power accounting for a 20% attrition rate (at 3 months post intervention follow-up).

Demographic characteristics of intervention and control group participants will be compared at baseline using t-tests for continuous variables and chi-square tests for categorical variables to assess whether participant characteristics were equivalent between groups. Adjustments for differences between groups will be done as needed. The primary outcomes, youth EBRBs, BMI-for-age percentile, and BMIz scores, will be evaluated by a multiple regression model (SAS software, SAS Institute Inc., Cary, NC) to test the null hypothesis that immediate post-intervention and 3-month post intervention outcomes are the same in the intervention and control groups. Baseline outcomes, covariates to adjust for baseline differences, potential confounders and site effect will be included in the regression model, to generate least squares adjusted mean changes, to generate a model comparing the intervention to control group. The secondary outcomes, self-reported parenting practices, will be evaluated by ANCOVA models to test the null hypotheses for each of the identified parenting behavior scale scores. Covariates to adjust for baseline differences, potential confounders and site effect will be included in the models to generate least squares adjusted mean changes for each group. A two-tailed significance level (alpha) of 0.05 will indicate statistically significant differences. The response rate expectation at 3 months post-intervention is 80% (based on 20% loss-to-follow up). This expected loss-to-follow up was accounted for in the power analysis for the primary outcome, which is based on 120 families per group. Multi-imputation of missing data is planned for the primary study outcome EBRBs. Chi-square tests and two-sample t-tests will be used to compare baseline characteristics between study completers and those lost to follow up to assess the potential for intervention effect bias due to study dropout. Secondary parenting outcome analyses will only include subjects with parenting practices scales data at the indicated data collection times for each analysis.

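### Part of the covariate set is tied to baseline differences found between randomized arms, and the covariate list for the parenting outcomes does not name the baseline score

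*Protocol*

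**What the plan says.** All of this is in the protocol's Statistical analysis section unless another place is named.

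- Demographic characteristics of the two arms are compared at baseline with t-tests (continuous) and chi-square tests (categorical), "to assess whether participant characteristics were equivalent between groups". The next sentence reads "Adjustments for differences between groups will be done as needed".
- Primary outcomes (youth behaviors, BMI-for-age percentile, BMI z-score) go into a multiple regression. Its terms are the baseline outcome, covariates for baseline differences, potential confounders and site.
- Secondary outcomes (parenting practice scales) go into ANCOVA models: "Covariates to adjust for baseline differences, potential confounders and site effect will be included in the models to generate least squares adjusted mean changes". This list matches the primary one except that the baseline outcome is absent.
- The Project summary lists baseline outcomes among the terms of the models, in the plural. The main outcome measures it names are youth behaviors and BMI-for-age percentile, not parenting practices.
- Under Intervention implementation, allocation follows baseline assessment, with a separate schedule for each site and randomized blocks of 2, 4 and 6: "Within each block, assignments will be balanced between Intervention and Control to ensure approximately equal group size".

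**The concern.** Assignment is made after baseline measurement, so any baseline difference between the arms as randomized arose by chance. A test of that difference checks a null hypothesis already known to be true. A non-significant result does not show equivalence, and a significant one says nothing about whether the variable predicts youth diet, activity or parenting scores. Covariate adjustment in a randomized trial earns its place through prognostic value. A rule driven by imbalance selects on something else, and the covariate set is settled only once the arms have been compared.

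The second issue is the difference between two parallel lists a few sentences apart. The primary list opens with the baseline outcome; the secondary list leaves it out but still reports adjusted mean changes. An analyst who follows the second list to the letter would analyse change without its baseline value and give up precision on every parenting scale.

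**Working it through.** **Inputs from the protocol.** Two-sided alpha of 0.05; a target difference of 0.5 SD in SSB intake; power of 90%; loss of 20% by the 3-month visit; 120 dyads per arm, so 120 × 0.8 = 96 per arm at 3 months. All are in the Statistical analysis section. The baseline-to-follow-up correlation and the covariate-outcome correlations are not given; both are assumed at 0.3, 0.5 and 0.7.

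**The plan's own figure.** n = 2(1.960 + 1.282)²/0.5² = 84.06, so 85 per arm. With 20% loss, 85/0.8 = 106.25, so 107. The plan has 120. With 96 completers the power is Φ(0.5/√(2/96) − 1.96) = 0.934. The stated 120 and 90% are therefore not reproduced exactly but are conservative. This does not bear on the present point; it supplies the 96 per arm used below.

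**How often a chance difference appears.** The Measurement section lists nine demographic items (age, sex, heritage, years in the U.S., country of birth, household composition, education, employment, food assistance). If they gave nine independent tests at 0.05, the chance of at least one significant result would be 1 − 0.95⁹ = 0.37. Independence is an assumption, and several items are plausibly correlated. For 5, 8, 10 or 12 independent tests the chance is 23%, 34%, 40% or 46%. This shows how readily the rule could fire; it does not measure bias.

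**What the rule costs.** 10,000 simulated trials per setting, 96 per arm, one normally distributed covariate, adjusted for either always or only when its baseline t-test is significant at 0.05:

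| Covariate-outcome correlation (assumed) | 0.3 | 0.5 | 0.7 |
|---|---|---|---|
| Type I error, adjust if significant | 0.045 | 0.041 | 0.037 |
| SE under the null, adjust if significant | 0.141 | 0.139 | 0.135 |
| SE under the null, always adjust | 0.137 | 0.125 | 0.103 |
| Power at 0.3 SD, adjust if significant | 0.55 | 0.54 | 0.55 |
| Power at 0.3 SD, always adjust | 0.59 | 0.66 | 0.82 |

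The 0.3 SD effect is illustrative. The test-driven rule recovers almost none of the available precision, and it does not inflate type I error.

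**If the baseline score really were left out of the secondary model.** With equal variances and correlation r, variance relative to ANCOVA is 2(1 − r)/(1 − r²) = 2/(1 + r) when change is analysed, and 1/(1 − r²) when the follow-up score is analysed. Power is Φ(0.3/(s√(2/96)) − 1.96), with s² = 2(1 − r) for change and 1 − r² for ANCOVA.

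| r (assumed) | 0.3 | 0.5 | 0.7 |
|---|---|---|---|
| Variance ratio, change vs ANCOVA | 1.54 | 1.33 | 1.18 |
| SE increase, change vs ANCOVA | 24% | 15% | 8% |
| SE increase, follow-up score vs ANCOVA | 5% | 15% | 40% |
| Power at 0.3 SD, change | 0.42 | 0.55 | 0.77 |
| Power at 0.3 SD, ANCOVA with baseline score | 0.59 | 0.67 | 0.83 |

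**The case against.** The strongest reply is that the text commits to less than it seems to.

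- No p-value threshold is stated. Adjustment driven by the tests is the natural reading, because the adjustment sentence follows directly on them, but it is not literal. Even so, the models name baseline differences as a reason for including covariates, so the link to imbalance stands without a threshold.
- Site is fixed in both models and the baseline outcome in the primary model, whatever the tests show. This stands. The primary estimate depends on chance imbalance only through the extra covariates, so the correlations in the simulation should be read there as what a covariate adds beyond baseline and site.
- Potential confounders form a separate category, so a balanced prognostic variable could still enter. This also stands, and naming those variables may be left to a statistical analysis plan. The point concerns the stated rule, not the missing names.
- For the secondary outcomes, ANCOVA in a trial with baseline and follow-up measures ordinarily means adjustment for the baseline value, and the Project summary points the same way, though its named outcomes are the youth measures. A reader might infer from the list that the baseline score is dropped. The documents do not support that; they show an inconsistency.

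A reader might also infer that outcome data steer the choice of covariates, or that false positives rise. The planned tests use arm and baseline data only, and the simulated type I error was 0.037 to 0.045. Discretion over the unnamed confounders was not simulated.

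**Conclusion.** The point holds in limited form. As written, part of the covariate set in both models rests on chance imbalance rather than prognostic value. The size depends on how prognostic the affected covariates are: with 96 per arm and an illustrative 0.3 SD effect, the loss is about 4 power points at a correlation of 0.3 (0.59 to 0.55) and 27 at 0.7 (0.82 to 0.55). These figures assume a single covariate and a 0.05 trigger.

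The secondary covariate list is inconsistent with the primary list, the ANCOVA label and the Project summary. The variance ratios of 1.54, 1.33 and 1.18 apply only if the baseline score is in fact left out and change is analysed, at assumed correlations of 0.3, 0.5 and 0.7. The planned 120 per arm is unaffected. The change is worth making because it costs almost nothing.

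**What to change.** In the Statistical analysis section, and in the matching sentence of the Project summary:

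1. Present baseline characteristics by arm descriptively. Delete the between-arm significance tests and the sentence that makes adjustment depend on differences. The separate comparison of completers with those lost to follow-up serves another purpose and can stay.
2. State that every primary and secondary model includes the baseline value of the outcome being analysed and site, the level at which the randomization schedules are generated. This settles the parenting-scale ANCOVA.
3. Add a small set of prognostic covariates, fixed before anyone analysing the data sees outcomes by arm. Youth age and sex are an example for the youth behavior outcomes. They are not needed for BMI-for-age percentile or z-score, which are already standardised for age and sex.
4. Put any adjustment prompted by observed imbalance in a labelled sensitivity analysis.

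The cost is wording only. Baseline outcomes, site, age and sex are already collected, and the sample size does not change.
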